**Figure 2 figure2:**
[figure not shown]
The Web- and mobile-based The-Optimal Lymph-Flow.

**Figure 3 figure3:**
[figure not shown]
Video instructions for daily exercises.

**Figure 4 figure4:**
[figure not shown]
Symptom reporting.

**Figure 5 figure5:**
[figure not shown]
Friendly reminder for daily exercises.

#### The-Optimal-Lymph-Flow Intervention Group (n=60)

Patients assigned to The-Optimal-Lymph-Flow intervention group will have access to the Web- and mobile-based The-Optimal-Lymph-Flow platform and they will learn about theprogram and daily exercises during the first in-person research visit. Patients will have access to the website contents of Lymphedema, Diagnosis of Lymphedema, Lymphatic System, Self-care, Daily Exercises, and Ask Experts. Patients will also have access to the 8 avatar videos that provide step-by-step instructions of daily exercises to promote lymph flow and optimize shoulder and limb mobility. In addition, the patients will be introduced to an app, and have the choice to use either the Web-based program or the app for daily exercises. However, patients *will not* have access to the section Arm Precautions since the participants in the intervention group will receive comparable information as in the Arm Precautions section, but with particular emphasis on “what to do,” rather than “what to avoid.”

#### Control Arm Precaution Group (n=60)

Patients assigned to the control Arm Precaution group will have access to the website section that emphasizes on precautionary lifestyle behaviors, such as avoidance of repetitive limb movement, lifting weighted objects, needle punctures, blood draw, and the use of compression garments for air travel in the affected limb [20,21]. Patients will have access to the following contents of the website: Lymphedema, Diagnosis of Lymphedema, Risk of Lymphedema, Lymphatic System, 3 avatar videos for Daily Exercises to promote limb mobility, and Arm Precautions. However, patients will not have access to The-Optimal-Lymph-Flow program, including Self-care*,* Daily Exercises to promote lymph flow, and 8 Avatar videos as well as Ask Experts that allows them to email to the researchers about their self-care. Patients will access to the Web- and mobile-based Arm Precaution program and learn about the program and daily exercises to promote limb mobility during the first in-person research visit.

#### Duration of Intervention

From the previous one-arm clinical trial and usability and feasibility studies on the Web- and mobile-based The-Optimal-Lymph-Flow [19,23], we estimate that it would take about 45-60 minutes for patients to learn all the sections of the program and about 15 minutes to learn the The-Optimal-Lymph-Flow exercises for the intervention group through 8 avatar videos. It takes about 5 minutes to perform a set of The-Optimal-Lymph-Flow daily exercises each time. We encourage patients in the intervention group to perform at least twice a day or more times of the exercises during the study period. Participants in the control group will have access to three limb mobility exercise avatar videos and it takes less than 3 minutes to perform a set of limb mobility exercises each time. Patients in the control group will be instructed to perform limb mobility exercises at least twice a day or more times during the study period.

### Data Collection

#### Data Collection Procedures

Data will be collected at baseline prior to intervention, and at week 12 post-intervention. Data collection at each time point will take approximately 30 minutes. Within one week of enrollment for the clinical trial, patients will have baseline assessment of pain and symptoms, limb volume difference, BMI, and quality of life. The follow-up assessment will occur at week 12 post intervention.

*Two In-Person Research Visits*: (1) prior to intervention there will be baseline assessment of pain and symptoms, limb volume difference, BMI, and quality of life; and (2) 12 weeks post-intervention assessment of pain and symptoms, limb volume difference, BMI, self-care behaviors, and quality of life.

*Two Online Assessments:* patients in the intervention and control group will receive an email that provides a link to assess pain and symptoms as well as quality of life at week 4 and week 8 post-intervention. Confidentiality of the patients will be protected for the online assessment since patients will use their study ID to access the online assessment.

#### Outcome Measures

*Demographic and Medical Information*: a structured tool is used to gather demographic and medical information and is verified through reviewing participants’ medical records [14,17,19]. The demographic and medical information will be considered as covariates, including expectation of the program, pain medications, age, surgeries, lymph nodes procedure, radiation, chemotherapy, time since surgery, time since lymphedema diagnosis, and hormonal therapy.

*Primary and Secondary Outcome Measures*: primary measure focuses on pain which is assessed during prior to the intervention and week 12 post-intervention in-person visit, as well as week 4 and 8 post-intervention online assessment. Secondary measures include symptoms, limb volume difference by infra-red perometer, BMI, quality of life related to pain. Limb volume difference by infra-red perometer and BMI are only measured prior to and week 12 post-intervention in-person visits. Symptoms and quality of life related to pain are assessed prior to and week 12 post-intervention in-person visit as well as week 4 and 8 post-intervention online assessment.

*Pain and Symptoms Related to Lymphedema:* the Lymphedema and Breast Cancer Symptom Experience Index is a valid and reliable self-report tool to assess pain, including aching, soreness, tenderness, as well as symptoms related to lymphedema (ie, arm swelling, breast swelling, chest wall swelling, heaviness, firmness, tightness, stiffness, burning, stabbing numbness, tenderness, stiffness, redness, blistering, and tingling (pins and needles) [14,17,19]. Each symptom can be treated as categorical variable by choosing a “Yes” or “No” to indicate the presence or absence of a given symptom. Each item can also be rated on a Likert-type scale from 0 (no presence of a given symptom) to 4 (greatest severity of a given symptom). Higher scores indicate more severe symptom presence. A response frame of last three months will be used for all participants to ensure the chronicity of symptom presence during the first in-person visit.

*Limb Volume Difference by Infra-Red Perometer*: perometry 350S will be performed on each arm as it is held horizontally. The perometer maps a 3-dimensional graph of the affected and non-affected extremities using numerous rectilinear light beams, and interfaces with a computer for data analysis and storage. A 3-dimensional limb image will be generated and limb volume will be calculated. This optoelectronic method has a standard deviation of 8.9 ml (arm), less than 0.5% of limb volume with repeated measuring [17,19] .

*Quality of life Related to Pain*: the Pain Impact Questionnaire (PIQ-6), a reliable and valid six question health survey, will be used to measure pain severity and the impact of pain on an individual's functional health and well-being. The PIQ-6 measures the severity of pain and its impact on work and leisure activities, as well as on emotional well-being within a variety of diseases and general populations. High PIQ-6 *T* scores indicate greater pain impact/worse health [21-23].

*Height, Body Weight, and BMI*: height will be measured to the nearest 0.1 cm with a portable stadiometer (Scale-Tronix 5002 Stand on Scale, Scale-Tronix Company, Carol Stream, IL, USA) without shoes [25]. An electrical device (InBody 520, Biospace Co, Ltd, Seoul, Korea) will be used to measure the participants’ body weight, BMI is calculated using the formula: weight (kg)/height (m^2^) [25].

*Practice of Self-Care Behaviors:* Risk Reduction Behavior Checklist is a structured self-report checklist that will be used to quantitatively and qualitatively assess patients’ practice of self-care behaviors at the study endpoint of 12-week after intervention [17,19]. The checklist include a list of self-care behaviors that promote lymph flow, eg, muscle-tightening deep breathing, muscle-tightening pumping, shoulder exercises, large muscle exercises, and having nutrition-balance and portion-appropriate diet, adequate hydration and sleep, as well as compression therapy for lymphedema.

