**Methods:**

A parallel RCT with a control-experimental, pre- and post-test, repeated-measures design is used in this study. A total of 120 patients will be randomized according to the occurrence of pain. Participants will be recruited face-to-face at the point of care during clinical visits. Participants in the intervention group will receive the Web- and mobile-based The-Optimal-Lymph-Flow intervention and will have access to and learn about the program during the first in-person research visit. Participants in the control group will receive the Web- and mobile-based Arm Precaution program and will have access to and learn about the program during the first in-person research visit. Participants will be encouraged to enhance their learning by accessing the program and following the daily exercises during the study period. Participants will have monthly online self-report of pain and symptoms at 4 and 8 weeks post-intervention. During the two in-person research visits prior to and 12 weeks post-intervention, participants will be measured for limb volume difference, BMI, and complete self-report of pain, symptoms, self-care behaviors, and QOL.

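### Self-care behaviours are scheduled at both visits in the abstract but only at week 12 in the Methods, which leaves the analysis with a post-randomisation covariate that the programme is meant to change

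*Protocol article*

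**What the plan says.** The Methods paragraph of the abstract opens its account of the visits with "During the two in-person research visits prior to and 12 weeks post-intervention" and says that participants then "complete self-report of pain, symptoms, self-care behaviors, and QOL". Read as written, self-care is reported before the intervention and again at week 12.

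The body of the article gives a different schedule. Data Collection Procedures lists the baseline content twice: "patients will have baseline assessment of pain and symptoms, limb volume difference, BMI, and quality of life", and, for the first visit, "prior to intervention there will be baseline assessment of pain and symptoms, limb volume difference, BMI, and quality of life". Self-care is in neither list. It appears only for the second visit: "12 weeks post-intervention assessment of pain and symptoms, limb volume difference, BMI, self-care behaviors, and quality of life". Outcome Measures agrees, placing the Risk Reduction Behavior Checklist so as to assess "practice of self-care behaviors at the study endpoint of 12-week after intervention". The items named for that checklist include diet, "adequate hydration and sleep, as well as compression therapy for lymphedema". The online assessments at weeks 4 and 8 cover pain, symptoms and quality of life, not self-care.

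The Analysis Plan gives self-care behaviours as one of its examples of covariates. It says that candidates for the models will be found from their bivariate correlation with treatment group, and that the models will carry fixed effects for whichever covariates are identified.

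**The concern.** The two schedules cannot both be carried out, and the more detailed one has no baseline. That matters mainly because of how the variable may be used. A self-care value taken at week 12 is downstream of randomisation, and changing it is the purpose of the programme. Conditioning the pain comparison on it means asking how the arms differ among women with the same self-care at week 12. Any benefit that works through self-care is then partly adjusted away.

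There is also a descriptive loss. Entry requires more than 3 months since surgery and admits women already treated for lymphedema. Some may already walk, do shoulder exercises or use compression. With one measurement after treatment, change within a woman cannot be calculated and results cannot be described by prior practice.

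**Working it through.** The article gives no figure to reproduce on this point, and none is needed. The check sets the relevant places side by side.

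1. **Number of self-care assessments per woman.** Abstract: before the intervention and week 12, so 2. Data Collection Procedures and Outcome Measures: week 12 only, so 0 at baseline and 1 after. Change from baseline needs both values. It can be calculated under the abstract and not under the Methods.

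2. **Other sources of a baseline value.** The demographic and medical covariates in Outcome Measures name neither self-care practice nor compression. The nearest item is time since lymphedema diagnosis. That list is open-ended and is checked against medical records, so earlier compression treatment might be captured there, but the article does not say so. Nothing listed would capture exercise, diet or sleep habits.

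3. **Whether the week-12 value would be selected.** The screen looks for correlation with treatment group. The intervention arm is taught the lymph-flow exercises; the control arm has no access to them (Control Arm Precaution Group). If the programme changes behaviour at all, the week-12 checklist will correlate with group. The screen therefore favours exactly the variable that should not be adjusted for, and the better the programme works on behaviour, the more surely it is chosen.

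4. **What adjustment would do.** The intended pathway runs from group to self-care to pain. Holding self-care fixed blocks that pathway, so the adjusted group difference reflects only what does not pass through the measured behaviours.

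5. **Loss of records.** A week-12 covariate is missing for women who have left by then. At the attrition the article allows for, that is 0.20 × 120 = 24 women. Their earlier pain reports would drop out of an adjusted model unless the covariate were imputed, which works against the stated reason for using mixed models.

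**The case against.** Much can be said on the other side, and most of it stands.

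- A reader might infer that without a baseline the trial cannot show that the programme changed behaviour. It can. Randomisation balances prior practice in expectation, so the week-12 difference between arms estimates the effect on behaviour.
- A reader might infer that a null result could never be traced to women who were already practising. That goes too far. The control arm's week-12 checklist gives a rough rate of practice without the programme.
- A reader might put a power loss on prior practice. The documents give no proportion of women already practising. Any such dilution would also occur whether or not it was recorded, so a baseline checklist would not restore power.
- Long-standing and newly started compression might still be told apart. The checklist's items are not shown, and it is described as both quantitative and qualitative.
- Self-care is not a declared primary or secondary outcome, and no hypothesis concerns it. The Methods are consistent among themselves; the abstract is the outlier.
- The baseline checklist has a cost. It names muscle-tightening breathing and pumping, which are withheld from controls, and would show them to controls before the trial starts. The effect would not be equal in the two arms, and it could weaken participant blinding. Keeping the checklist to week 12 is a defensible choice.
- The covariate problem could be solved by not adjusting, with no new assessment. That is true, and it is the alternative offered in the fix.

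One technical limit also applies. The plan judges the treatment effect by the group-by-time interaction. If week-12 self-care entered a linear model only as a person-level main effect and data were complete, that interaction would be largely unaffected. The distortion arises where the covariate is crossed with time or made time-varying, or where the arms are compared at week 12. The article does not fix which of these will be used.

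**Conclusion.** The point holds as a contradiction in the schedule with a consequence for the analysis. The abstract and the Methods disagree on whether self-care is measured at baseline. Under the Methods, the only self-care value available as a covariate is a post-randomisation one that the programme is meant to change. Adjusting for it could remove part of the treatment effect on pain. Change within women and description by prior practice are lost for all 120 participants.

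The size of any distortion cannot be calculated from the article. It depends on how strongly the programme shifts behaviour, how strongly behaviour relates to pain, and how the covariate enters the model. The conclusion assumes that the Methods schedule is the one followed and that the self-care behaviours in the covariate list are among the candidates screened. The missing baseline does not by itself bias the primary comparison: the unadjusted pain comparison and the week-12 comparison of behaviour between arms remain valid. The change should be made, but the design is not at risk without it.

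**What to change.** Reconcile the abstract, Data Collection Procedures and Outcome Measures. The preferred way is to follow the abstract: give the Risk Reduction Behavior Checklist, with its compression item, at the first in-person visit before the programme is shown, and again at week 12. In the Analysis Plan, state that only the baseline self-care value may serve as an adjustment covariate and that the week-12 value never may. Report the week-12 value by arm as a behaviour or adherence result, with change from baseline.

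The cost is a few minutes on an existing form at an existing visit. The drawback is that controls may become aware of the lymph-flow exercises, which could slightly narrow the contrast between arms. If the sponsor keeps week 12 only for that reason, the abstract should be corrected to match and self-care behaviours removed from the covariates. Either route removes the contradiction and the risk to the pain comparison; only the first also allows change within women to be reported.

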### Statistical Analysis

#### Primary Endpoint

The primary endpoint for the study is absence of pain or pain reduction reported by the participants at week 12 post-intervention.

#### Sample Size and Power Calculations

We will enroll a total of 120 participants: 60 participants in The-Optimal-Lymph-Flow intervention and 60 participants in the Arm Precaution control group to account for a potential attrition of 20%, which has been observed in the prior studies in breast cancer survivors [10]. This will yield an adequate analytic sample size. Even with 20% attrition based on a 2 sample 2-sided *t* test with alpha=.05 and power of 90%, we can detect a difference of 0.7 standard deviations in the difference between the presence of pain in the intervention group compared to the control group at 8 weeks or at 12 weeks. The projected sample size will also provide sufficient statistical power for mixed regression models. For linear mixed models of continuous outcomes (eg, pain ratings), statistical power will exceed 80% to detect a medium effect, assuming a constant group effect, correlations of r=.5 between observations, alpha=.05, and compound symmetry of the covariance structure.

For binary outcomes, based on the three repeated observations with a conservative estimate for the assumed correlation of r=0.5 between observations, alpha=.05, sample size of n=50 per treatment arm will have power of 80% to detect odds ratios of the difference between groups ranging from 2.6 to 3.5 (small to medium effects).

Adequacy of sample size will be monitored during the analyses in three ways: (1) assessing sufficiency to estimate the number of model parameters identified by preliminary analyses; (2) examining model fit indices (eg, intra-class correlation coefficient to assess fit of random effects) to ensure data adequately support models generated, and (3) assessing the adequacy to accurately estimate model parameters by generating confidence intervals.

#### Analysis Plan

We will summarize graphically and numerically the distributions of pain, aching, soreness, tenderness, other symptoms related to lymph fluid accumulation, limb volume differences, BMI, and quality of life as well as covariates (such as medication for pain, age, or education and treatment variable and limb volume and self-care behaviors). The proportion of individuals experiencing pain, aching, soreness, tenderness will be compared between the intervention and control group over time, as will the mean severity ratings and associated quality of life scores. Mean comparisons of number of reported symptoms, limb volume, and BMI will be conducted between the intervention and control group as well as over time.

Bivariate relationships between the variables and treatment group will be assessed using point-biserial correlations and phi coefficients to identify potential covariates for inclusion into statistical models. Linear mixed effects models will be used to analyze continuous outcomes (eg, ratings pain, aching, soreness, tenderness, symptom ratings, and quality of life) and generalized linear mixed models will be used to analyze binary outcomes (presence of pain, aching, soreness, tenderness, and total scores of quality of life). These models will incorporate fixed effects for time, group, and any identified covariates. As indicated by preliminary models to estimate variance effects, models will include random effects for subject-specific slopes and intercepts. A statistically significant fixed effect for group by time interaction will indicate a treatment effect, with the direction of difference determined from mean values. Models will be compared for goodness of fit and modifications to link functions, distributional form, and correlation structure will be made as necessary.

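### Covariates are screened on their association with treatment group, with no baseline-only limit, so variables changed by the intervention can enter the efficacy models and bias the group comparison

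*Protocol article*

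**What the plan says.** The Analysis Plan first lists what will be summarised, including "covariates (such as medication for pain, age, or education and treatment variable and limb volume and self-care behaviors". It then gives the selection rule: "Bivariate relationships between the variables and treatment group will be assessed using point-biserial correlations and phi coefficients to identify potential covariates" for the models. No threshold is stated, and the variables to be screened are not defined or limited to baseline. What the screen finds goes into the outcome models: "These models will incorporate fixed effects for time, group, and any identified covariates". The treatment effect is read from one term: "A statistically significant fixed effect for group by time interaction will indicate a treatment effect".

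On timing, Outcome Measures says that a checklist will "assess patients’ practice of self-care behaviors at the study endpoint of 12-week after intervention". Data Collection Procedures likewise lists self-care at the 12-week visit and not at baseline, although the abstract mentions it for both in-person visits. The checklist items are the exercises, diet, hydration and sleep habits that Table 1 sets out as the intervention. Limb volume difference is a secondary outcome, measured at baseline and week 12.

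Outcome Measures also has its own covariate list. It omits self-care behaviors and limb volume, and ends with "time since surgery, time since lymphedema diagnosis, and hormonal therapy".

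**The concern.** Randomisation already determines how baseline variables relate to group: any association is chance. A screen on that association therefore says nothing about prognosis, which is the reason to adjust in a trial. For a variable measured after randomisation, association with group is what one expects if the intervention works. The rule thus favours consequences of treatment.

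Conditioning on a consequence of treatment that lies on the path to pain removes the part of the effect that runs through it. The adjusted coefficient no longer estimates the randomised comparison, and an effective programme can look weaker than it is. The primary endpoint is pain at week 12, so bias in the adjusted week-12 contrast matters.

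**Working it through.** **1. The plan's own figure.** Sample Size and Power Calculations enrols 60 per arm with 20% attrition: 60 × 0.8 = 48 per arm, 96 in all. For a two-sided t test at alpha .05 and 90% power, the detectable difference is about (1.960 + 1.282) × √(2/48) = 0.66 SD by the normal formula and 0.669 SD by the exact t calculation. Power at 0.7 SD is 92.4%. The stated 0.7 SD is reproduced, slightly conservatively, and serves below as the total effect.

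**2. What the screen selects.** The cut-off is not given; p<.05 is assumed. With n = 96 and true correlation r with group, the Fisher approximation gives P(selected) = Φ(z − 1.96) + Φ(−z − 1.96), where z = atanh(r) × √93.

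| r with group | 0 | 0.2 | 0.3 | 0.4 | 0.5 |
|---|---|---|---|---|---|
| P(selected) | 0.05 | 0.50 | 0.85 | 0.98 | 1.00 |

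A between-arm shift of s SD corresponds to r = (s/2)/√(1 + s²/4): 0.24 for s = 0.5, 0.37 for s = 0.8 and 0.51 for s = 1.2. The documents give no value for s.

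**3. What adjustment does, by model.** Simulation: 48 per arm, visits at weeks 0, 4, 8 and 12, compound symmetry with r = 0.5 (the plan's structure), total week-12 effect 0.7 SD growing linearly, complete data, 400 trials per setting, s from 0.5 to 1.2. The share of the effect running through self-care is assumed. Estimates are rounded sizes in SD.

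| Mediated share | 0% | 25% | 50% | 75% | 100% |
|---|---|---|---|---|---|
| No self-care term | 0.70 | 0.70 | 0.70 | 0.70 | 0.70 |
| Week-12 ANCOVA with self-care | 0.70 | 0.52 | 0.35 | 0.18 | 0.00 |
| Mixed model, self-care acting over time: group by time | 0.70 | 0.52 | 0.35 | 0.18 | 0.00 |
| Mixed model, self-care as main effect only: group by time | 0.70 | 0.70 | 0.70 | 0.70 | 0.70 |

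The two attenuated rows follow 0.7 × (1 − mediated share). In the last row the interaction equals the unadjusted one in every setting, because a covariate that is constant within a participant cannot alter change over time in this model.

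**4. The week-12 contrast in that same main-effect model.** The contrast is the group term plus the interaction, and the group term does move. The covariate takes out the mediated effect averaged over the visits. At 50% mediated, the mediated part at week 12 is 0.5 × 0.7 = 0.35 SD.
- Linear growth: the average over visits is (0 + 1/3 + 2/3 + 1)/4 = 0.5 of that, so the contrast is 0.70 − 0.175 = 0.525 SD.
- Constant after baseline: the average is 3/4, so 0.70 − 0.2625 = 0.4375 SD.
- Post-baseline visits only, constant group effect: 0.70 − 0.35 = 0.35 SD.

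Simulation agrees (about 0.51, 0.43 and 0.36 SD). The third case matters because the plan's mixed-model power statement assumes a constant group effect.

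**5. Missing values.** A covariate that exists only at week 12 is absent for anyone who leaves earlier. At the planned attrition that is up to 120 × 0.2 = 24 participants. Unless it is imputed, their week-4 and week-8 reports fall out of the model, contrary to the advantage claimed in the missing-data section.

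**6. The two lists.** The Analysis Plan list has self-care and limb volume; the Outcome Measures list has neither. The latter includes time since lymphedema diagnosis, which has no value for participants never diagnosed, whom Study Population admits.

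**The case against.** A reader might infer that the models will adjust away the treatment effect. The documents do not support that. The planned test is the group by time interaction, covariates enter as fixed effects, and no covariate-by-time term is planned. A self-care score measured once and entered as a main effect leaves that interaction unchanged in the linear model with complete data. This stands; it was not tested for the binary mixed model or with missing scores.

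Nor is inclusion certain. Self-care and limb volume are named in a sentence about descriptive summaries, the screen finds only potential covariates, and the abstract leaves room for a baseline self-care measure. Baseline limb volume would be a legitimate covariate. Controls also receive exercise videos and are told to exercise at least twice daily, so the gap in self-care between arms may be modest. All of this stands.

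A single-time-point regression gives starker numbers. With a 0.5 SD total effect, a 1 SD self-care gap and half the effect mediated (all assumed), the estimate falls to 0.25 SD and power from 68% to 20%. These illustrate a week-12 adjusted comparison only, not the planned interaction test.

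Finally, one might say that entering time since diagnosis drops everyone without lymphedema. No coding rule is given and multiple imputation is mentioned, so that goes too far; the variable is simply undefined for them.

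None of this defends the selection rule, which uses the wrong criterion and has no baseline limit.

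**Conclusion.** The point holds in limited form and should be fixed. The screen ignores prognosis and favours variables that treatment has changed. Admitting one can bias the group term and any adjusted week-12 contrast, often toward no effect. If the variable varies with time or acts over time, as limb volume at both visits could, it can also attenuate the interaction. The size depends on the mediated share, which the documents do not give: from nothing at 0% to the whole effect at 100% in a week-12 adjusted comparison. At 50% of a 0.7 SD effect, the week-12 contrast would be about 0.35 to 0.53 SD, depending on the model and the time course. The figures also rest on an assumed p<.05 cut-off, an assumed shift in self-care between arms, and complete data. The disagreement between the two covariate lists needs no assumption; it leaves the adjustment set open to choice after the data are seen.

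**What to change.** - Delete the screen against treatment group.
- Pre-specify a short set of baseline covariates chosen for prognosis, for example the baseline value of the outcome, baseline pain medication, lymphedema history (yes/no) in place of time since diagnosis, and time since surgery. Baseline limb volume is acceptable.
- State that self-care behaviors and post-baseline limb volume are excluded as covariates from the efficacy models, and use them only in a separate mediation or adherence analysis.
- Give one covariate list and make Outcome Measures and the Analysis Plan agree with it. State whether self-care is measured at baseline, since the abstract and Methods differ.

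The cost is a change of wording. No new data are needed.
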